Exploratory study aim 2 of PP3 is to assess risk factors for different levels of active suicidality, consisting of active suicidal ideation (S-STS item 3), active suicidality with preparatory action (S-STS 12), self-injurious behavior without suicidal intent (S-STS item 13), or suicide attempts (S-STS item 14).

Exploratory study hypothesis 2: Active suicidality as defined above is associated with (i) slower rate of remission of suicidal symptoms after baseline, greater baseline severity of (ii) depressive symptoms, (iii) manic symptoms (below the threshold of (hypo)mania as part of MDD), (iv) anxiety symptoms, (v) anger and hostility, (vi) quality of life impairment (vii) global illness symptoms, and (viii) suicidality, (ix) higher number of lifetime depressive episodes, (x) duration of current depressive episode, (xi) index admission as part of psychiatric emergencies, (xii) higher non-adherence to pharmacological and non-pharmacological treatments, (xiii) comorbid borderline personality disorder, and (xiv) comorbid substance use diagnosis.

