Hypotheses 3A and 3C will be analyzed by means of methods for count data, such as Poisson or Negative Binomial models, depending on whether overdispersion is present in the data or not. The dependent variable will be overall duration of PASI during the 6-month observation period and the independent variable of main interest will be time to remission of suicidal symptoms after baseline.

Hypotheses 3B and 3D will be analyzed by using Cox proportional hazard models, where the dependent variable will be time-to-first-recurrence of PASI and the independent variable of main interest will be time to remission of suicidal symptoms after baseline.

Further independent variables for regression analysis will include patient, illness, and treatment variables, including severity of depressive symptoms (MADRS, Quality of Life in Depression Scale (QIDS-S) [79]), manic symptoms (YMRS), anxiety (BAI), anger/hostility (STAXI, AF-BP), global illness symptoms (CGI-S), quality of life (EQ-5-DL), and suicidality (S-STS); presence of psychiatric emergencies; number of lifetime depressive episodes; duration of current depressive episode; nonadherence to pharmacological and nonpharmacological treatments; and comorbid borderline personality and substance abuse. Additionally, a random factor accounting for clustering of patients in centers will be added to the models.

Assuming a minimum requirement of 10 patients per predictor variable in regression analyses [91–93] and approximately 20 independent patient, illness, and treatment variables that would be tested as potential correlates of time to remission of suicidality, we estimated that a sample size of at least 200 would be required.

Additionally, as a secondary analysis, we will divide patients into two groups using the median time up to the first S-STS value of zero, which are either below or above the median time to first complete remission of suicidality.

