Furthermore, comparisons between the slower and faster remitting group of continuous variables will be performed using multiple comparison procedures (MCPs) with 3 measurement time points (T1, T2, and T4). Because only the primary outcome and very limited other parameters are collected by telephone at T3, data at T3 are not included in these analyses. Because the timing at T2 (hospital discharge) is variable, and this timing is not independent of the outcome measured, the duration between T1 and T2 is included as a covariate in the analyses. Cross-group comparisons of dichotomized or categorical variables are performed using chi-square statistics. For ease of comparison, continuous outcomes, such as depressive symptoms and medication use are calculated. All analyses are two-sided, with alpha = 0.05. Due to the exploratory nature of the study, no adjustment for multiplicity between different endpoints is conducted. Hence, p-values and confidence intervals need to be interpreted in a hypothesis-generating manner. In addition, multivariable regression analysis with backward selection will be performed to identify independent moderators or mediators of continuous and categorical outcomes, respectively. Moreover, missing continuous data will be treated using multiple imputation using chained equations and random effects for the clustering of patients in different centers.

Among the exploratory objectives, the patient, illness, and treatment factors that influence the risk of different levels of active suicidality are identified: i) active suicidality (S-STS item 3), ii) active suicidality with preparatory action (S-STS item 12), iii) self-injurious behavior without suicidal intent (S-STS item 13), and iv) suicide attempt (S-STS item 14) during the observation period of inpatient treatment and within 6 months of study inclusion (T1). Target parameters i)-iv) are associated with slower initial resolution of suicidality (lower than median time to S-STS score = 0); and with: Depressive symptom severity (MADRS, QIDS-S), manic symptoms (YMRS), anxiety (BAI), anger/hostility (STAXI, AF-BP), and global illness symptoms (CGI-S); higher number of lifetime depressive episodes; more frequent psychiatric emergencies; longer duration of current depressive episode; non-adherence to pharmacological and non-pharmacological treatments; comorbid borderline personality; and substance abuse diagnoses.

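### The secondary and exploratory PP3 analyses cut time to remission of suicidality at the sample median, which discards information, and the text reverses which half is the slower one

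*Protocol article*

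**What the plan says.** All quotes are from the protocol article, section Sample size and statistical analyses, unless stated otherwise.

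- Main models (hypotheses 3A to 3D): "the independent variable of main interest will be time to remission of suicidal symptoms after baseline". No cut-point is given.
- Secondary analysis: "we will divide patients into two groups using the median time up to the first S-STS value of zero". Patients fall below or above that median.
- Use of the groups: "comparisons between the slower and faster remitting group of continuous variables will be performed using multiple comparison procedures (MCPs"), over T1, T2 and T4, with the T1 to T2 interval as a covariate. Categorical variables are compared by chi-square.
- Exploratory aim 2: the four levels of active suicidality are related to "slower initial resolution of suicidality (lower than median time to S-STS score = 0"). The hypothesis itself, in Aims and hypotheses, speaks of a "slower rate of remission of suicidal symptoms after baseline", with no cut.
- Inference: "All analyses are two-sided, with alpha = 0.05". There is no multiplicity adjustment, and "p-values and confidence intervals need to be interpreted in a hypothesis-generating manner".

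**The concern.** Time to the first S-STS of zero is an ordered quantity with more than two levels, and the plan's own main models treat it as one. Cutting it at the median makes opposites of two patients who remit just before and just after the cut. It also treats remission just after the median the same as remission at month 6. The cut is a property of this sample, so slow and fast have no fixed meaning in another cohort. The article gives no clinical reason for it.

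The groups are not only descriptive, because they are tested at a two-sided 5% level. In exploratory aim 2 the median is the only stated form of remission speed when it is related to preparatory action, self-injury and suicide attempts. A real association would be easier to miss there.

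Two further problems follow from the split:
- A patient lost while still suicidal before the median cannot be put in either group without an assumption. The article reports 34% dropout in PP3.
- Slower remission means a longer time to zero, yet the parenthesis in aim 2 calls it lower than the median. Coded literally, the predictor would have the wrong sign.

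**Working it through.** **The plan's own figures.** PP3 enrols 315 with 34% attrition: 315 × 0.66 = 207.9, which reproduces the stated 208. The required minimum is 10 patients × about 20 predictors = 200. Neither figure depends on the median split. The article states no power, effect size or distribution of time to remission, so those below are assumptions.

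**Information kept by the split.** For a linear effect of an exactly observed time X, the share kept is the squared correlation f² between X and its above-median indicator D (SD of D = 0.5).

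- Uniform on 0 to 1: cov = 0.375 − 0.25 = 0.125; f = 0.125 / (0.2887 × 0.5) = 0.866; f² = 0.75. Lost: 25%.
- Normal: cov = 0.3989; f = 0.3989 / 0.5 = 0.798; f² = 2/π = 0.637. Lost: 36%.
- Exponential: cov = 0.5 × ln 2; f = ln 2 = 0.693; f² = 0.480. Lost: 52%.

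On 208 patients this is like analysing 208 × 0.75 = 156, 208 × 0.637 = 132 or 208 × 0.480 = 100.

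**Power, if the uncut analysis had 80%.** The non-centrality is 1.960 + 0.842 = 2.802. Power after the split = Φ(2.802 × f − 1.960).

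- Uniform: Φ(0.466) = 67.9%, a loss of 12.1 points.
- Normal: Φ(0.275) = 60.8%, a loss of 19.2 points.
- Exponential: Φ(−0.018) = 49.3%, a loss of 30.7 points.

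**Dependence on the effect.** With n = 208, power = Φ(√205 × atanh(r × f) − 1.960), where f = 1 if uncut:

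| r | uncut | split, normal | split, exponential | loss in points |
|---|---|---|---|---|
| 0.05 | 10.7% | 8.2% | 7.2% | 2.4 / 3.5 |
| 0.10 | 30.0% | 20.7% | 16.7% | 9.3 / 13.3 |
| 0.20 | 82.7% | 63.5% | 51.5% | 19.2 / 31.2 |
| 0.30 | 99.3% | 93.8% | 85.6% | 5.6 / 13.8 |
| 0.40 | about 100% | 99.7% | 98.3% | 0.3 / 1.7 |

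(Losses were taken before rounding.) Simulation at n = 208 with r = 0.20 agrees: 19.6 points lost (normal) and 29.9 (exponential). Simulated binary outcomes with odds ratios of 1.3 to 2.0 per SD and prevalence 10% to 40% lose about 4 to 36 points. For example, with a normal time, odds ratio 1.5 and prevalence 20%, power is 63.7% uncut and 43.9% split.

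**Allowing for how time is observed.** After T1, Table 1 schedules the S-STS only at T2, T3 and T4. A simulation with r = 0.193 used a log-normal time seen only at a variable discharge date, month 3 and month 6, with never-remitters ranked last. It gave 45% to 73% power for the uncut analysis and a loss of about 12 to 19 points from the split. Those inputs are also assumed, so the result is indicative.

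**Direction.** Aims and hypotheses: "slower rate of remission of suicidal symptoms after baseline". Statistical section: "slower initial resolution of suicidality (lower than median time to S-STS score = 0"). A slower rate is a longer time, so the two statements point in opposite directions.

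**The case against.** The strongest defence is that nothing central rests on the split. It is labelled secondary or serves exploratory aims, the p-values are declared hypothesis-generating, and the 3A to 3D models use the time itself. That stands and limits the severity. It does not justify the split, since an exploratory analysis exists to pick up signals.

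Second, the article bases its sample size on about 20 variables tested as correlates of time to remission and mentions multivariable regression with backward selection. A reader might infer that the split is the only way the study will describe slow remitters. The documents do not support that: a regression on time to remission is indicated, though its model is not named, and an article may leave that to the full protocol.

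Third, the power figures assume exactly observed times. The article acknowledges intermittent interviews and recall bias, so the 31-point end is not supported for the data as they will be collected. A loss of about 12 to 19 points remained in the coarse-time simulation.

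Fourth, a reader might infer residual confounding from adjusting for a two-level remission covariate. No section describes such an adjustment, so that is not claimed.

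Finally, a median grouping can at least classify as slow a patient followed to month 6 who never reaches zero, whereas a log time or spline is undefined for that patient. This is correct and shapes the fix.

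**Conclusion.** The point holds as a minor one. The secondary slower-versus-faster tests and exploratory aim 2 use a sample-median cut that discards information available at no cost. The loss is about 25%, 36% or 52% for uniform, normal or exponential times, or about 12, 19 or 31 points from an assumed 80%. These figures require a linear effect and exactly observed times. The loss is smaller for very weak or strong effects, and its size in this study is uncertain because of the visit schedule and recall.

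A reader might take from this a flat loss of about a third of the information and 12 to 31 points. The documents do not support that: about a third is the normal case alone, the range spans three distributions, and neither the distributions nor the 80% is in the article. Nor are hypotheses 3A to 3D or the size of 315 enrolled and 208 followed weakened.

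The reversed wording for slower resolution is a plain error that does not depend on any assumption.

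**What to change.** In Sample size and statistical analyses:

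1. For T1 characteristics, make the inferential analysis a survival model of time to first S-STS of zero, interval-censored or discrete-time if dates are known only to the visit. Use continuous covariates, a centre random effect, and censoring of non-remitters at last contact.
2. In exploratory aim 2, enter remission as a time-updated covariate, or in another uncut form that states how never-remitters are handled, in place of above or below the median.
3. Keep the median groups for descriptive tables and plots, including the courses over T1, T2 and T4, without tests.
4. Correct the parenthesis so that slower resolution means a longer time to zero, and reconcile it with the exploratory hypothesis. If the median label stays in any table, state how patients lost before the median are classified.

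The cost is wording and some extra programming, with no new data, visits or patients. A hazard ratio or a time-updated effect is less simple to present than two groups; the retained descriptive tables cover that.

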## Background

Major depressive disorder (MDD) is among the most common mental disorders worldwide and has been increasing in recent decades [1]. The lifetime prevalence of MDD exceeds 10% [2, 3]. MDD criteria include depressed mood, diminished interest or pleasure, weight or appetite increase or decrease, insomnia or hypersomnia, psychomotor agitation or retardation, fatigue or loss of energy, feelings of worthlessness or inappropriate guilt, diminished ability to think or concentrate, or indecisiveness, and recurrent thoughts of death or recurrent suicidal ideation [4].

Patients with MDD are more frequently female, older [5, 6] and most often cared for in primary care settings [7, 8], where most antidepressants, mostly selective serotonin reuptake inhibitors (SSRIs) [9, 10] are prescribed, with escalation to secondary or inpatient care in cases of more severe acute or dangerous clinical scenarios. MDD requiring hospitalization may follow those demographics but has also been associated with treatment-resistant depression, occurring in approx. 20% of people with MDD [11], presence of passive or active suicidal ideation [12, 13], and lifetime history of a suicide attempt, which is present in approximately 20% of people with MDD [14].

Suicide is a significant public health problem. The World Health Organization (WHO) has reported more than 700,000 deaths per year (1/100) worldwide due to suicide in 2019. Among 15–29-year olds, suicide is the fourth leading cause of death, and 58% of suicides occurred before the age of 50 years [15]. Suicide attempts are generally preceded by various forms of suicidal ideation. Often, national surveys do not measure passive suicidal ideation, but only active suicidal ideation [16–18]. One possible reason for this is that suicidality has historically been thought to progress along a continuum, from passive suicidal ideation (i.e., thoughts about death or a desire for death in general), to active suicidal ideation (i.e., thoughts of killing oneself) to suicidal plans, to suicidal behavior [19, 20]. However, recent studies suggest that there is no such continuum and that the association between passive suicidality and suicidal behavior and between active suicidality and suicidal behavior is comparable [12, 13, 19]. Therefore, studies must include passive suicidal ideation.

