MDD is one of the disorders most strongly associated with suicidality [21]. For example, in patients with MDD, at least passive suicidality is present in about 50% [22], lifetime prevalence of suicide attempts is 31% [23], and lifetime prevalence of completed suicide is up to 10% [24–26], more than 20 times higher than in the general population [27]. In fact, in a meta-analysis, next to previous suicidal behaviors, severe depressive symptoms was the only other factor that was significantly associated with suicidal ideation, suicide attempt as well as death by suicide [28]. This high co-occurrence of depressed mood with suicidality justifies the inclusion of suicidal thoughts and actions as a criterion for depressive disorder in the Classification of Mental and Behavioural Disorders (ICD-10) [29] and Diagnostic and Statistical Manual of Mental Disorders (DSM-5) [4].

Few studies have examined features that are correlated with depression with and without suicidality, including worthlessness, guilt, despair, depressive and manic symptoms, inner restlessness and agitation, sleep disturbances, previous suicidal behavior, hopelessness, rumination, social withdrawal, lack of activity, crying, self-injurious behavior, feelings of loss of control, experiences of derealization, and course of depression [30–34]. Furthermore, individual studies have identified relatively few factors that can influence the course of depression with suicidality, e.g. severity of depression, comorbid disorders, including anxiety, hopelessness, anger, misuse of alcohol and drugs, and personality disorders [34–37].

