### Primary inclusion criteria

Inclusion criteria for PP1 are (i) male and female patients; (ii) aged between 18 and 75 years; (iii) admitted to a psychiatric inpatient unit, and (iv) having an ICD-10-based chart diagnosis of single depressive episode (F32) or recurrent depressive episode (F33).

Inclusion criteria for PP2 (originating from PP1) are (i) male and female patients; (ii) aged between 18 and 75 years; (iii) admitted to a psychiatric inpatient unit; (iv) having an ICD-10-based *clinical* diagnosis of a single or recurrent depressive episode of *at least moderate severity*, including single depressive episode, moderate episode (F32.1), single depressive episode, severe episode without psychotic symptoms (F32.2), single depressive episode, severe episode with psychotic symptoms (F32.3), recurrent depressive episode, currently moderate episode (F33.1), recurrent depressive episode, currently severe episode without psychotic symptoms (F33.2), and recurrent depressive episode, currently severe episode with psychotic symptoms (F33.3); (v) *clinically* diagnosed suicidality that persists for ≥ 48 h after inpatient admission; and (vi) sufficient German language skills to understand the purpose and procedures of the study and cooperate with the study procedures; and (vii) providing written informed consent to participate in the study.

Inclusion criteria for PP3 (originating from PP2) are (i) male and female patients; (ii) aged between 18 and 75 years; (iii) admitted to a psychiatric inpatient unit; (iv) having an ICD-10-based *research* diagnosis according to the Mini-International Neuropsychiatric Interview (M.I.N.I.) [71] of a single or recurrent depressive episode of *at least moderate severity* (for details, see PP2 above); (v) *research interview-based* suicidality with a score ≥ 1 on item 2 (passive suicidality) OR item 3 (active suicidality) using the Sheehan–Suicidality Tracking Scale (S-STS) [21]; (vi) written informed consent to participate in the study.

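### Faster and slower remitters are defined by suicidality reaching zero and then compared on depressive symptoms; if the depression totals include a suicidal-thoughts item, part of any difference may be the grouping variable itself

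*Protocol article*

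**What the plan says.** All references are to the Protocol article.

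- **Grouping.** Sample size and statistical analyses, PP3, secondary analysis: "we will divide patients into two groups using the median time up to the first S-STS value of zero". The halves lie below and above that median.
- **Comparison.** Same section: "comparisons between the slower and faster remitting group of continuous variables will be performed using multiple comparison procedures (MCPs) with 3 measurement time points". The time points are T1, T2 (discharge) and T4 (month 6). T3 is left out because little is collected by telephone.
- **Outcome.** Same section: "continuous outcomes, such as depressive symptoms and medication use are calculated". This sentence names no scale. Elsewhere the section gives MADRS and QIDS-S as the measures of depressive severity. It mentions no score without a suicide item.
- **Construct.** The Background lists "recurrent thoughts of death or recurrent suicidal ideation" among the MDD criteria. It adds that the co-occurrence of depressed mood and suicidality "justifies the inclusion of suicidal thoughts and actions as a criterion for depressive disorder" in ICD-10 and DSM-5.
- **Safeguard.** The time from T1 to T2 enters as a covariate, because discharge timing varies and is not independent of the outcome.
- **Status.** The comparison is secondary. Tests are two-sided at 0.05 without multiplicity adjustment, and p-values are to be read as hypothesis-generating.

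**The concern.** The grouping variable is suicidality, and the outcome is a construct that the article itself describes as including suicidality. If a depression total carries a suicidal-thoughts item, patients who have not reached S-STS zero at a visit will tend to score higher on that item, and so on the total, even if every other depressive symptom is the same in both halves.

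The visit schedule makes this plausible at discharge. After baseline, Table 1 schedules the S-STS only at T2, T3 and T4. T2 is therefore usually the first visit at which a zero can be recorded, and patients not at zero then will tend to land in the slower half. Patients who never reach zero would presumably also sit there, so some overlap can remain at T4. Nothing is built in by definition at T1, because every PP3 patient enters with at least passive or active suicidality scored 1 or more (Primary inclusion criteria).

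What is at stake is interpretation. A reader would take a difference in depressive symptoms to mean something beyond suicidality, and one total cannot separate the two.

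**Working it through.** **The plan's own figure.** 315 × (1 − 0.34) = 207.9, which agrees with the stated 208 patients with data at month 6. A median split gives 208 / 2 = 104 per half.

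**Inputs that the article does not give (assumed).**
- The depression total contains one suicidal-thoughts item.
- The SD is 8 to 10.
- Slower remitters still suicidal at T2 average 2 or 3 points on that item; all other patients score 0 on it.
- No other depressive symptom differs between the halves.

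**Step 1: from a gap in the item to a rejection rate.** With gap g in the group means, SD s and n per half:

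noncentrality = (g / s) × √(n / 2) = (g / s) × √52 = 7.21 × g / s

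rejection = P(|Z + noncentrality| > 1.96)

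For g = 1 and s = 10 the noncentrality is 0.72 and the rejection rate 0.11. For g = 3 and s = 8 it is 2.70 and 0.77.

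| Gap (points) | Standardised difference (SD 10 to 8) | Rejection (SD 10 to 8) |
|---|---|---|
| 0.5 | 0.05–0.06 | 0.07 |
| 1 | 0.10–0.13 | 0.11–0.15 |
| 2 | 0.20–0.25 | 0.30–0.44 |
| 3 | 0.30–0.38 | 0.58–0.77 |

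**Step 2: what gap is plausible.** Gap = share of slower remitters still suicidal at T2 × their mean item score. For example, 0.10 × 2 = 0.2 and 0.50 × 3 = 1.5. The rejection rates below come from simulation: 2,000 runs per setting, 104 per half, with SD 8 or 10 applied to the rest of the scale.

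| Slower remitters still suicidal at T2 | Gap (points) | Rejection, item kept |
|---|---|---|
| 0% | 0 | about 5–6% |
| 10% | 0.2–0.3 | about 5–6% |
| 30% | 0.6–0.9 | about 7–14% |
| 50% | 1.0–1.5 | about 12–28% |
| 100% | 2.0–3.0 | about 32–77% |

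With the item removed, rejection stayed at about 4–6% in every setting, that is, near nominal.

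**Step 3: sample size at T2.** The 104 is a month-6 figure, and the article places the higher dropout between discharge and month 6. More patients may therefore be present at T2. At the upper limit of 157 per half (315 / 2, rounded down), a gap of 1 gives 0.14–0.20 and a gap of 2 gives 0.43–0.60 (SD 10 to 8).

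**Step 4: does the covariate help?** Adjusting for T1–T2 duration deals with when discharge occurs. Of two patients with the same length of stay, one at S-STS zero and one not, the second will still tend to score higher on the shared item.

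**The case against.** The strongest objection is that the article never shows the scales' item content. The Background describes diagnostic criteria, not questionnaire items. That stands: the point is conditional, and if a total has no such item, its built-in part is zero.

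Second, the sentence on outcomes names no scale or total, and scoring detail may be left to an analysis plan that is not shown. That is fair as to omission. The article does, however, fix both the grouping and the outcome, and the overlap follows from that pairing.

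Third, group membership is not the same as status at T2. A slower remitter can reach zero before discharge, a faster one can have relapsed, and T2 may fall after T3 (Trial design). The S-STS also records preparatory action and self-injury without suicidal intent, so a non-zero score need not mean suicidal thoughts. A reader might infer that slower remitters must score above the floor at T2 and faster ones must not; the documents support only a tendency. Nor do they give any figure for the share still suicidal at discharge, so the upper rejection rates cannot be read as expected values.

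Fourth, the analysis is secondary and hypothesis-generating. That limits the weight of the point. But the label is given as the reason for not adjusting for multiplicity, and it does not answer an overlap that pushes the difference in one direction.

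A reader might also extend the point to hypotheses 3C/3D and exploratory aim 2. The documents do not support that. S-STS is already in the variable list for the 3C/3D models. Exploratory hypothesis 2 (Aims and hypotheses) lists baseline suicidality as a predictor, although the later list in the statistics section leaves it out.

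**Conclusion.** The point holds in conditional form and for one secondary analysis only. If the depression totals contain a suicidal-thoughts item, part of a slower/faster difference at T2, and possibly at T4, may reflect the grouping variable, and the stated covariate does not remove it. On the assumed values the built-in part runs from nil or negligible (0–10% of slower remitters still suicidal at T2: a gap of up to 0.3 points and near-nominal rejection) to material (half: about 12–28% rejection; all: about 32–77%). Where the trial will fall in that range cannot be told from the article. The result rests on the assumed item, SD, item scores and equality of all other symptoms. The primary analyses of 3A to 3D are not affected.

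**What to change.** First check the instruments for a suicidal-thoughts item. Then, in the slower/faster comparison, analyse MADRS, QIDS-S and any other depression total used both with and without that item. State in advance that a difference will be attributed to depressive symptoms beyond suicidality only if it persists in the item-free score. Reporting the number in each half not at S-STS zero at T2 and T4 would show the reader how far the overlap can reach.

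The cost is a little extra analysis of data already collected, provided item scores are stored. Item-free totals are not comparable with published totals, which is why the standard totals stay beside them. No change is needed for 3C/3D or exploratory aim 2.
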